### Study procedure

The intervention program will last one academic year. After randomization, meetings will be held with teachers of each classroom to describe the specific program to be carried out by each classroom without telling them which group they belong to (control or intervention) and to set the dates of sessions and evaluation procedures. Teachers of the intervention groups will receive some training, as they are models for children. All intervention and control sessions will be held by the same nutritionist, and data collection at baseline (T0: September), during (T1: January) and after (T2: June) intervention will be performed by the same researcher. To check any long-term effect, the measurements will be carried out one year after the end of the intervention (T3: June). Diagram of the study timeline is presented in Fig. 1

**Fig. 1 Fig1:**
[figure not shown]
Diagram of the study timeline

.

### Intervention design

Following baseline data collection and randomization, the intervention group will start receiving program lessons every 15 days. Intervention group will receive 14 sessions of one hour over an academic year, from a nutritionist.

A multidisciplinary team designed the program. All materials, sessions and the program design are based on TPB and are respectful of gender, culture or religion. This theory states that people’s behavior is determined by their intentions, which in turn are influenced by attitudes, subjective norms and perceived behavioral control [24].Behavior: the action of eating FV.Intention: perceived likelihood of eating FV.Attitude: favorable or unfavorable judgments about eating FV. These judgments are determined by people’s beliefs, experiences and knowledge.Subjective norms: beliefs that most people who are important to children either approve or disapprove of them eating FV.Perceived behavioral control: perceptions of how much control they have over the behavior (action of eating FV).

In this study, these different variables are worked as described in Table 1.

**Table 1 Tab1:** Techniques to work behavioral determinants

Determinants of TPB	Behavior change technique	Example of how it is applied in the program
Attitude	Provide information on the behavior-health relationship	More FV ... “Why?” “Because they are healthy” They contribute ... “Fiber helps your gut work!”
	Work on positive / negative consequences of behavior (action / inaction)	The consequences of behavior are worked on according to the health benefits of various components of VF “To Do or Not To Do”
	Provide information about the relationship between pleasure and behavior	More information given about we eat what we like More FV ... “Which?” “The ones you like!”
	Work the ability to get pleasure through eating FV	The capacity of discriminating sensorial analysis is worked on, encouraging exploration “Explore with your senses” “Enjoy the ones you like!”
Subjective norms	Provide information about others behavior	Record the consumption of FV of all classmates on a sheet that all can see (“Fruitmeter”)
Perceived behavioral control	Work on instructions to increase autonomy or ability	Instructions are provided to make it easy reaching goals such as 5 a day: “If you eat fruit for breakfast... you’re already in way 1 out of 3!” “Food and dinners are times ... with vegetables on your plates!”
	Work on situations that promote autonomy	Situations related to autonomy that promote the consumption of FV are practiced: participating in processes involved in producing, selling and preparing FV, e.g. cultivating, choosing and buying, cooking). “Get to know the orchard” “Participate! Choose and buy” “Have fun cooking”

Combining different theories in the program was discarded. This choice is based in a meta-analysis that analyzed the influence of behavioral theories on FV intervention effectiveness among children that found no association between the number of theories and consumption [27].

To make the program more effective, sessions were designed based on learning taxonomies [31], active learning methodologies and persuasion techniques (ELM: Elaboration Likelihood Model) [32]. All sessions have their own script for the nutritionist involved and all the scripts have the same structure (objectives, methodology, argument and resources). The script will be followed by the nutritionist with the aid of an audiovisual presentation, sheets for students, sheets for families, a goal-diary, FV’s folder, album and stickers, and material for specific sessions (e.g. FV as rewards at the end of each session and the “Fruitmeter”).

The proposed strategy has three axes of action: a) school activities, b) outside activities and c) home activities.School activities: Nine sessions will be held within the school (7 within the classroom and 2 FV cooking sessions in the dining room). Every month a “Fruitmeter” session will take place. In this activity, each classroom should write down their group FV mean intake using a tool called the “Fruitmeter”, which works by social pressure (subjective norms) to reach the objective of eating more FV. The “Fruitmeter” has poster format and will be hung in each classroom.Outside activities: Two visits to local product markets and two visits to local farmers. The last session will be held in a local theatre as the final FV program party.Home activities: a goal-diary which works with objectives related to FV consumption, e.g. to try a new vegetable this week or to eat fruit for breakfast three times per week, will be filled in at home with participants’ families. All worksheets that children use at school will be noted when they are reviewed at home with families.

The control group only will receive two one-hour lessons during the academic year with general information about the benefits of FV intake. These sessions will be given by a nutritionist and will not be based on behavioral theories.

### Outcomes

#### Primary outcome: Quantitative outcome

FV intake: FV (excluding potatoes and legumes) consumption will be measured by a validated self-fulfilling food record [33]. It provides information about standard servings of FV intake for 7 days, and it must be filled out by parents or legal guardians. To control self-completed food record data reliability, a researcher will make telephonic 24-h dietary recalls (goal-standard) on one randomly chosen day during the week in which the record is being filled.

#### Secondary outcomes: Qualitative outcomes

Determinants of eating behavior: evolution of determinants proposed (attitude, subjective norms and perceived behavioral control) will be analyzed by a questionnaire designed according to bibliographic proposals [34]. Each determinant will be measured by a minimum of 3 items that will be answered by children marking a number on a 1–5 scale from “totally disagree” to “totally agree”. Validity of the survey will be checked by its internal consistency (Cronbach’s alpha).
Social demographic outcomes and families’ FV consumption habits: data will be collected by a questionnaire designed by the Department of Sociology 2 of the University of the Basque Country to obtain the following information:
Parental educational attainmentParental employment situationTheir perceived importance of their children’s FV intakeTheir level of knowledge concerning FV recommended intakeFV availability and accessibility at homeWhere children have their main mealChildren’s TV watching habits during mealsParents’ FV consumption habits.

Codified surveys will be sent by means of the children inside codified sealed envelopes. These will be filled out at home by parents and returned to school. Questionnaires of behavior determinants of behavior will be completed in 20 min by children at school under the supervision of a nutritionist. All the questionnaires will be completed at the three times described previously (T0, T1, T2) during the academic year and one year after intervention will be finished (T3).

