**Methods:**

Eligible classrooms within schools from Vitoria-Gasteiz (Basque Country, Spain) will be randomly assigned to the intervention (classrooms *n* = 4; children *n* = 86) or control (classrooms *n* = 4; children *n* = 86) group. The intervention group will receive 14 sessions of 60 min during an academic year (October to June). These sessions, designed by a multidisciplinary team, are based on TPB and are directed at modifying determinants of behavior (attitudes, subjective norms, perceived behavioral control and intention of consumption), and intake of FV itself. Both the process and the evolution of consumption and determinants of behavior will be evaluated (before, during, shortly after and a year after) using validated surveys, 7 day food records, 24 h reminders and questionnaires.

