### Hypothesis

An intervention program to increase FV intake in schoolchildren aged 8 to 10 and based on TPB will produce changes in attitude, subjective norms, perceived behavioral control and intention of eating FV, which in turn will modify behavior, thus increasing FV intake.

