### Statistical analysis

Descriptive statistics will be carried out to describe baseline characteristics of intervention and control group to assure comparability between groups.

Intra-group and inter-group FV intake differences at T0, T1, T2 and T3, will be analyzed by Student’s *t* test or non-parametric tests (Wilcoxon signed-rank test and Mann–Whitney U test). The same tests will be carried out to study the evolution of determinants of eating behavior (attitude, subjective norms, perceived behavioral control and intention) at different times.

To understand the relationship between determinants of behavior and behavior itself (FV consumption), multiple linear regression and structural equation modeling (SEM) analysis will be done at different times. Covariance of classic relationship of TPB determinants will be proposed. It will allow us to check the validity of the proposed model, as well as the influence of each determinant on the others and its significance. Changing models will be made by using difference on TPB determinants between different times.

Model validity will be established by comparative fit index (CFI), root mean square-error of approximation (RMSEA) and chi square/degrees of freedom (χ2/df). A good model will be determined by high values of CFI (> 0.90), low values of RMSEA (< 0.10) and χ2/df values from 1 to 3 [35, 36].

Multiple linear regression will be used to study the effect of social demographic variables in the effectiveness of the intervention.

Statistical analyses will be made using STATA 14.0, IBM-SPSS 24.0 and AMOS 24.0 statistical software. IC of 95% and significance level of *p* < 0.05 will be assumed.

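### The structural equation models, as described, give the randomised arm no role, so they do not estimate the programme's indirect effect that the hypothesis asserts; the list of measured constructs also needs reconciling on intention

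*Protocol article*

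**What the plan says.** The Hypothesis section of the protocol article states that the programme "will produce changes in attitude, subjective norms, perceived behavioral control and intention of eating FV, which in turn will modify behavior". The Intervention design section places intention between the other three constructs and behaviour.

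The Objectives section separates two links of this chain. Secondary objective (ii) is the programme's impact on the determinants. Secondary objective (iii) is the association of the determinants with intake.

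On measurement, the Secondary outcomes section says that "evolution of determinants proposed (attitude, subjective norms and perceived behavioral control) will be analyzed by a questionnaire" and adds that "Each determinant will be measured by a minimum of 3 items". Intention is not in that list. The Methods paragraph of the abstract describes sessions aimed at "modifying determinants of behavior (attitudes, subjective norms, perceived behavioral control and intention of consumption" and says that "Both the process and the evolution of consumption and determinants of behavior will be evaluated" at four times.

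On analysis, the Statistical analysis section applies t tests or rank tests, within and between groups, to intake and to the "determinants of eating behavior (attitude, subjective norms, perceived behavioral control and intention) at different times". Regression and SEM are then introduced to relate determinants to intake, using the classic relationships of the Theory of Planned Behavior (TPB), and "Changing models will be made by using difference on TPB determinants between different times". Fit thresholds are given. No sentence places the randomised arm in these models. The Discussion says that the SEM will let the authors gauge how the determinants influence the change in eating habit, and presents this as a new advance.

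**The concern.** A hypothesis worded as "which in turn will modify behavior, thus increasing FV intake" is a mediation statement. To examine it, one needs the effect of arm on each determinant, the effect of each determinant on intake given arm, and the combination of the two with an interval. The analyses described supply the first as stand-alone group comparisons and the second as a model in which arm is not mentioned. Nothing joins them.

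At stake is the interpretation of the trial's theory-based claim. A determinant and intake can move together because the programme moved both by separate routes, because one drives the other, or because something else drives both. A model without arm does not separate the first explanation from the second. Good values of CFI, RMSEA or chi-square/df would not help, since the fit of a determinant-intake model says nothing about an indirect effect of arm.

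The second issue concerns intention. It is the last step before behaviour in the chosen theory and it is named for analysis, but the only description of the child questionnaire omits it.

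**Working it through.** **No plan figure to reproduce for this point.** The article gives no sample size or effect size for the SEM. Its 86 per arm belongs to the primary comparison. It reproduces with a two-sided t test (sidedness assumed) at d = 0.5, alpha 0.05 and 90% power: 85.03, rounded up to 86. It has no bearing on mediation.

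**Step 1. Constructs, place by place.**

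| Section | Constructs named | Intention? |
|---|---|---|
| Abstract, Methods | 4 | yes |
| Hypothesis | 4 | yes |
| Secondary outcomes (questionnaire) | 3 | no |
| Statistical analysis | 4 | yes |

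The outcome section is the odd one out. The text does not settle whether its parenthesis is incomplete or intention was not measured.

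**Step 2. Where arm enters.**

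| Link in the hypothesis | Analysis described | Arm included? |
|---|---|---|
| programme to determinants | between-group tests, objective (ii) | yes |
| determinants to intake | regression, SEM, change models, objective (iii) | not stated |
| programme to determinants to intake | none | – |

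**Step 3. Why the first two rows do not add up to the third.** In the simplest linear case, let a be the effect of arm on a determinant, b the slope of intake on that determinant given arm, and c' the remaining effect of arm. The total effect is c = c' + a × b. The slope b must be conditional on arm. A slope from a model that combines the arms and omits arm is not b.

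**Step 4. Size of the difference, by illustration.** Assumptions, none from the documents: two equal arms combined in one model, unit variance within arm, no within-arm relation between determinant and intake (true b = 0), and the same shift of s SD in both from the programme.

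- Covariance in the combined data = 0.25 × s²
- Variance of each variable = 1 + 0.25 × s²
- Correlation, here equal to the slope = 0.25 s² / (1 + 0.25 s²)

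| s | Covariance | Variance | Correlation | Apparent indirect effect (s × slope) | True indirect effect |
|---|---|---|---|---|---|
| 0.5 | 0.0625 | 1.0625 | 0.059 | 0.5 × 0.059 = 0.029 SD | 0 |
| 1.0 | 0.25 | 1.25 | 0.20 | 1.0 × 0.20 = 0.20 SD | 0 |

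At 0.5 the spurious correlation explains 0.059² = 0.35% of variance, and the apparent indirect effect is 0.029/0.5, about 6% of the total effect. At 1.0 it is 20%.

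**Step 5. Precision.** Arm is assigned to 8 classrooms in two groups, so the arm-to-determinant path rests on about 8 − 2 = 6 degrees of freedom between classrooms. Any indirect effect will be imprecise.

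**The case against.** The strongest reply has four parts.

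*The SEM matches its objective.* Objective (iii) asks only for association, objective (ii) is covered by the between-group tests, and no listed objective asks for an indirect effect. This is true, and it makes the point an improvement and not an error in serving those objectives. It does not dispose of the hypothesis, which states the joined path.

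*A condensed article may leave the arm term to a fuller document.* This is fair, and it limits the point to the models as described. But the article does give the SEM's purpose, structure, change models and fit criteria, and the Discussion draws on them.

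*Intention is probably measured.* A reader might infer from the outcome section that there are no data on intention. The documents do not show that. The analysis section commits to testing intention over time, the abstract counts it as a determinant whose course will be evaluated, and the item rule covers each determinant. An incomplete parenthesis is a plausible explanation. What stands is an inconsistency.

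*The distortion is small and new items are no remedy.* At 0.5 SD, which is also the trial's planning effect size for intake, the spurious correlation is only about 0.06. The figure of 0.20 needs shifts twice as large in both variables. Adding items for past visits is also largely impossible. With the study ending in December 2018 and T3 in a June one year after T2, T3 is June 2018 at the latest, T2 June 2017 and T0 about September 2016. Both arguments stand, and the fix relies on data already planned.

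**Conclusion.** The point holds in a limited form. The article states a mediation hypothesis and describes models that, as written, estimate determinant-intake associations with no stated role for the randomised arm. The programme's indirect effect is not estimated, and the Discussion's statement about the process of change should not be read as the result of a tested causal chain.

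Three stronger readings are not supported:

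- **That the chain cannot be tested.** If intention was on the questionnaire, the T0 to T3 data on arm, determinants and intake would allow a mediation model. The article simply does not describe one.
- **That the SEM pools the arms.** The text does not say so. A model fitted within arm or by group is compatible with it, and the figures of 0.06 and 0.20 apply only if arms are combined without an arm term, under the assumed shifts.
- **That adding arm would establish causation.** Arm is randomised but the determinants are not, so the determinant-to-intake path remains open to common causes.

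The primary comparison of intake is unaffected. This is a cheap improvement to the secondary, explanatory analysis, together with an inconsistency on intention that must be reconciled.

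**What to change.** 1. In the change SEM, enter randomised arm as an exogenous variable with paths to each determinant, to intention and to FV intake. Report the direct and indirect effects of arm, with intervals that account for classroom clustering.
2. State that the determinant-to-intake path remains observational and that indirect effects will be imprecise with 8 classrooms. Word the Discussion accordingly. If the arm term is not added, limit the claim to association.
3. Reconcile the Secondary outcomes section (three constructs) with the abstract, Hypothesis and Statistical analysis sections (four) by stating whether intention was on the questionnaire at T0, T1, T2 and T3. If it was, add it to the list. If it was not, remove intention from the planned analyses and limit the conclusions to the three measured constructs.

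The cost is one more variable in the model, slightly more analysis and reporting work, and a few lines of text. No new data collection is needed. The downside is that the indirect effects will probably have wide intervals.

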### Objectives

The main objective of this study is to evaluate the effectiveness of an intervention program based on TPB in increasing FV intake in schoolchildren aged 8 to 10.

Secondary objectives of the study are (i) to evaluate the change in FV intake in the study population after intervention, (ii) to examine the impact of the intervention program on behavioral determinants, (iii) to analyze the association of the behavioral determinants with FV intake, and (iv) to study the relationship between social demographic variables and the effectiveness of the program.

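### Cronbach's alpha is a reliability measure and cannot establish the validity of the determinants questionnaire; per determinant it does not show whether the determinants are distinct

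*Protocol article*

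**What the plan says.** The Secondary outcomes section of the protocol article describes a questionnaire built for this study from proposals in the literature. It is to measure attitude, norms and perceived control: "Each determinant will be measured by a minimum of 3 items", each answered on a 1 to 5 agreement scale. The section then names the property to be established and the means of establishing it: "Validity of the survey will be checked by its internal consistency", with Cronbach's alpha given as the measure. It states no alpha cut-off and no other validity check for this instrument.

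The determinants are then used as separate variables. Objective (iii) is "to analyze the association of the behavioral determinants with FV intake". The Statistical analysis section plans tests over time for four determinants, adding intention: "determinants of eating behavior (attitude, subjective norms, perceived behavioral control and intention) at different times". It also plans multiple linear regression and SEM to examine how each determinant influences the others. The SEM has its own criteria (CFI above 0.90, RMSEA below 0.10, chi-square/df from 1 to 3), stated for the validity of the model and not of the questionnaire.

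**The concern.** Alpha summarises how strongly the items of a scale correlate with one another. It does not show what the items measure. Computed per determinant, it uses no information about items belonging to other determinants, so it cannot show that attitude, norms and perceived control are different things. The check named therefore cannot deliver the property named.

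The theory behind the intervention needs separable determinants. If two scales largely measure one thing, their separate regression or path coefficients cannot be read as separate influences. The Discussion section intends to use those influences to design more focused programs. The respondents are children of 8 to 10 and all items share one response format, so separation is better shown than presumed.

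**Working it through.** The article gives no figure on this point, so there is none to reproduce.

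**Inputs**
- Items per determinant: k = 3, the stated minimum (Secondary outcomes).
- Determinants: 3, as listed in that section, so 9 items in all.
- Inter-item correlation within a determinant, r: not given; assumed 0.3 to 0.6.
- True correlation between determinants, φ: not given; varied from 0 (fully distinct) to 1 (one construct).
- Alpha pass mark: not given; a conventional 0.70 is assumed where one is needed.
- N = 172 (Sample size), used only in the simulations.

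**1. Alpha per determinant.** For three items with common correlation r, alpha = 3r/(1 + 2r).
- r = 0.3: 0.9/1.6 = 0.56
- r = 0.4: 1.2/1.8 = 0.67
- r = 0.5: 1.5/2.0 = 0.75
- r = 0.6: 1.8/2.2 = 0.82

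φ does not appear in the formula, so these values are the same for φ = 0 and φ = 1. Alpha reaches 0.70 when 3r = 0.70(1 + 2r), that is r = 0.70/1.6 = 0.44.

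**2. Scale scores if there is only one construct.** Two three-item sums then correlate 9r/(3 + 6r) = 3r/(1 + 2r), for example 0.75 at r = 0.5. Divided by the reliability of 0.75, this is 1.0. A correlation corrected for unreliability therefore detects the overlap that alpha misses.

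**3. Alpha for the whole survey**, the literal reading of the sentence. For nine items, alpha = (9/8)(1 − 9/T), with T = 9 + 18r + 54rφ. At r = 0.5:
- φ = 0: T = 18, alpha = 0.56
- φ = 0.3: T = 26.1, alpha = 0.74
- φ = 0.6: T = 34.2, alpha = 0.83
- φ = 1: T = 45, alpha = 0.90

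On this reading alpha is highest when the determinants collapse into one.

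**4. Simulation with 5-point items, N = 172, 1,000 samples per setting.** The table gives the share of samples in which all three determinant alphas reached 0.70.

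| Latent r | Distinct (φ = 0) | One construct (φ = 1) |
|---|---|---|
| 0.5 | 28.2% | 37.8% |
| 0.6 | 97.5% | 98.7% |

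The result depends mainly on r and very little on whether the determinants are distinct. The mean between-scale correlation corrected for unreliability was about 0.00, 0.30, 0.60 and 1.00 for φ = 0, 0.3, 0.6 and 1.

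**5. Would the SEM criteria catch it?** A correlated three-factor model was fitted to data from one construct (N = 172, r = 0.5, 60 runs). Median CFI was 0.999, median RMSEA 0.012 and median chi-square/df 1.02. CFI above 0.90, RMSEA below 0.10 and chi-square/df of at most 3 were met in all 60 runs. The lower limit of 1 on chi-square/df was not tested. The fit is good because one construct is the special case of this model with all factor correlations equal to 1. The estimated factor correlation was indeed about 1.00, but the article sets no criterion on it.

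The simulations ignore clustering by classroom.

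**The case against.** A journal article condenses the full protocol. Factorial or discriminant checks could stand in a document not shown, and the literature source for the items may lend them some support. That is fair as far as missing detail goes, and the absence of a factor analysis is not in itself the point. The point is a positive statement that names validity and assigns alpha to check it.

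The strongest rebuttal is the SEM. If it uses latent factors, which the article does not specify, its output would include factor correlations, and a value near 1 would expose the overlap. This stands in part: an attentive analyst would see the problem. The stated criteria, however, would not require action on it.

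Several stronger readings are tempting, and the document does not support them:
- **That the check would pass whatever the structure.** No cut-off is stated, and at r of 0.3 or 0.4 a three-item scale falls below 0.70 whether or not the determinants are distinct.
- **That the determinants do overlap.** The document gives no data on this; the single-construct case is hypothetical.
- **That the comparisons between arms under objective (ii) are invalid.** A test of a score remains a valid test of that score; only the name given to the score is in doubt.
- **That the abstract falsely calls this instrument validated.** Its wording, "using validated surveys, 7 day food records, 24 h reminders and questionnaires", lists surveys and questionnaires separately and does not clearly refer to this one.

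**Conclusion.** The point holds as a minor one. The article assigns to a reliability measure the task of establishing validity. Per determinant, alpha is the same for distinct and for identical determinants: 0.56 to 0.82 across assumed inter-item correlations of 0.3 to 0.6. The SEM fit criteria do not make up for this. The figures rest on three items per determinant, equal inter-item correlations and, for any statement about passing, an assumed mark of 0.70.

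The consequence is limited to reading separate coefficients under objective (iii) and in the SEM, and to the construct labels under objective (ii). The primary outcome, intake from the food record, does not depend on this questionnaire.

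**What to change.** In Secondary outcomes, describe alpha as a measure of reliability and report it for each determinant.

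For validity, before the determinant regressions and the SEM, fit a confirmatory factor model to the T0 items in AMOS, which the article already lists. Include intention if it is measured by items; it is analysed but not among the determinants that the questionnaire section lists. Compare the model with one factor per determinant against a one-factor model, and report the factor correlations against a limit fixed before the data are examined. Where two determinants exceed that limit, do not interpret their separate coefficients. Pooling them is better kept as a sensitivity analysis, since the hypothesis names them separately.

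The cost is one extra analysis on items that the plan collects at T0 anyway, with no new software. The downside is that some claims about single determinants may have to be withheld.
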